### 2.5. Randomization and blinding

This trail will use random assignment concealment. Participants who provide informed consent and meet the inclusion criteria will be randomly assigned in a 1:1 ratio to treatment and control groups. Randomization will be based on random numbers generated by the computer. Independent researchers will prepare the distribution in an opaque envelope containing the distribution sequence number and are responsible for concealing the distribution sequence. Due to the specificity of the intervention, double-blinding was impossible. Outcome assessors, data curators will be unaware of treatment assignments.

## 3. Interventions

### 3.1. Basic interventions

Patients are advised to eat a light diet, quit smoking and alcohol, keep warm appropriately, maintain a comfortable mood, and avoid overwork during the treatment.

### 3.2. Drug intervention

#### 3.2.1. Treatment group.

Patients in this group will take TDSJ orally. The composition of TDSJ are as follows: astragalus 30g, coix seed 30g, pueraria lobata 30g, dipsacus asperoides 20g, taxilli herba 20g, rhizoma drynariae 20g, eucommia 20g, rehmannia glutinosa 15g, pyrola 15g, paeoniae alba 15g, achyranthes bidentata 20g, ground beetle 10g, ligusticum chuanxiong 20g, angelica sinensis 15g, safflower 10g, clematis chinensis 20g, angelicae pubescentis radix 10g, corydalis yanhusuo 20g, licorice 6g. The drug will be uniformly provided by the Chinese Pharmacy of the First Affiliated Hospital of Henan University of Chinese Medicine, decocted in water, 400mL per payment, 1 payment per day, divided in the morning and evening, oral for 8 weeks.

#### 3.2.2. Control group.

Patients in this group will take celecoxib capsules in combination with thalidomide tablets. Celecoxib capsules are provided by Sichuan Guowei Pharmaceutical Co., Ltd., Sinopharm H20203357, specification 0.2g*20 capsules, 1 capsule in the morning and evening, oral for 8 weeks; Thalidomide tablets are provided by Changzhou Pharmaceutical Factory Co., Ltd., Sinopharm H32026129, specification 50mg*20 tablets, 2 tablets in the evening, oral for 8 weeks.

### 3.3. Combined treatment regulations

If the subjects meet the inclusion criteria, and the patients with other diseases need to continue to use the drug in the clinical trial, or if they really need to add other drugs or treatment methods due to the needs of the disease treatment, the drugs used should be recorded in the case report form in detail. name (or treatment method), dosage, frequency of administration, time of administration, etc. The drugs and treatment methods that must be taken in combination with other diseases must be recorded in detail in the combined medication table. If disease progresses during the study, participants can withdraw from the study and use other treatments. This case will be treated as an excluded case and the patient will be asked to complete relevant examinations and assessments as far as possible.

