#### 2.3.3. Inclusion criteria.

The inclusion criteria are as follows: Meet the Western medical diagnostic standards of AS; TCM dialectic is cold-dampness obstruction type; 18 to 40 years old, male or female; Women of childbearing age ascertain to be non-pregnant and had no pregnancy plans for the duration of the trial; Did not take any AS treatment drugs in the 1 month period before receiving treatment; Voluntarily participate in this trial and agree to enter the clinical study, sign the informed consent form.

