#### 2.3.4. Exclusion criteria.

The exclusion criteria are as follows: Patients with other rheumatic immune system diseases; Those with serious diseases such as heart, brain, lung, liver, kidney, tumor, infection or hematopoietic system; Patients who are taking other Chinese medicine treatment for certain diseases; Lactating or pregnant women; Those who are allergic to the drugs in this test; Patients with mental disorders who cannot communicate effectively; Active peptic ulcer/bleeding, sulfa allergy; Patients with severe heart failure; Patients with perioperative pain during coronary artery bypass graft.

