## 4. Outcome measures

### 4.1. Primary outcome

Visual analogue scale, bath ankylosing spondylitis disease activity index, bath ankylosing spondylitis functional index, and TCM syndrome scores will be primary indicators, which will be tested at 0th and 8th weeks of treatment.

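### Section 3.3 can be read as allowing added treatment for AS on record-keeping alone, with no stated rule for the week-8 primary scores that follow it

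*Protocol article*

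**What the plan says.** Section 3.3 of the protocol article is the trial's rule on co-treatment. It covers three situations:

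- **Drugs for other diseases.** "The drugs and treatment methods that must be taken in combination with other diseases must be recorded in detail in the combined medication table".
- **Added treatment.** "if they really need to add other drugs or treatment methods due to the needs of the disease treatment, the drugs used should be recorded". The details go into the case report form; no other consequence is stated.
- **Progression.** "If disease progresses during the study, participants can withdraw from the study and use other treatments". The next sentence adds: "This case will be treated as an excluded case", although examinations and assessments are still sought as far as possible.

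Two eligibility rules bear on the same treatments. Section 2.3.3 requires that patients "Did not take any AS treatment drugs in the 1 month period before receiving treatment". Section 2.3.4 excludes "Patients who are taking other Chinese medicine treatment for certain diseases". Both apply at entry.

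In section 3.2.2, "Patients in this group will take celecoxib capsules in combination with thalidomide tablets"; the decoction in section 3.2.1 contains no NSAID. Section 4.1 states that the pain scale, BASDAI, BASFI and "TCM syndrome scores will be primary indicators, which will be tested at 0th and 8th weeks of treatment". Section 2.5 says double-blinding was impossible and masks outcome assessors and data curators only. Section 4.5 bases efficacy and safety analyses on intent-to-treat in all randomised participants.

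**The concern.** The entry criteria protect attribution at baseline: no recent AS drugs and no other Chinese medicine. The primary scores are produced over the following 8 weeks, and no stated rule carries that protection forward. If a participant adds a drug that acts on pain, stiffness or function and stays in the trial, the week-8 score reflects both the assigned treatment and the addition, yet it counts for the assigned arm.

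The arms are not placed alike. Controls already take celecoxib, whereas an NSAID added in the TDSJ arm would be of the same class as part of the comparator. Without double-blinding, the decision to add something can depend on the arm. Masked assessors do not help, because the score itself has already changed.

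A worsening participant may also have two routes. One is to add treatment and remain, so that the score counts. The other is to withdraw and become an excluded case, so that a poor result may drop out. Progression is not defined in the article, withdrawal is optional, and the second route does not fit an analysis of everyone randomised.

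**Working it through.** **1. The passages side by side.**

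| Point | At entry | During the 8 weeks |
|---|---|---|
| AS drugs | None in the preceding month (2.3.3) | No stated restriction; additions recorded if really needed (3.3) |
| Other Chinese medicine | Users excluded (2.3.4) | No stated restriction (3.3) |
| Progression | – | Optional withdrawal, then an excluded case (3.3); all randomised analysed (4.5) |

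The need condition in section 3.3 has no criterion, and the article does not say how scores after an addition are handled.

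**2. The plan's own sample size.** Inputs from section 2.4: 78% versus 43%, two-sided α = 0.05. No power is stated. With unpooled variance and 90% power:

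n = (1.960 + 1.282)² × (0.78 × 0.22 + 0.43 × 0.57) / 0.35² = 35.7, so 36 per group.

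Allowing for 10% loss, 36 / 0.9 = 40 per group, 80 in total. The stated figures reproduce. Power at 36 per group is 90.2% unpooled and 87.6% with the pooled-variance test used in step 4.

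**3. Illustration on a continuous score, excess in the TDSJ arm.** The documents give neither an add-on rate nor an add-on effect. *Assumed:* no true difference between arms; a net extra 10–30% of TDSJ participants add something worth 0.5–0.8 SD.

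- Standard error at 36 per group: √(2/36) = 0.236 SD.
- Difference needed for significance: 1.994 × 0.236 = 0.47 SD.
- Bias = share × effect: 0.10 × 0.5 = 0.05 SD, up to 0.30 × 0.8 = 0.24 SD.
- Two-sided rejection probability (normal approximation), with δ = bias / 0.236: Φ(−1.96 + δ) + Φ(−1.96 − δ).
  - δ = 0.21: 0.040 + 0.015 = 5.5%.
  - δ = 1.02: 0.173 + 0.001 = 17.5%.

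**4. Illustration on the effective rates of section 2.4, both directions.** *Assumed:* half of the non-responders who take an add-on become responders; 36 per group; pooled-variance test.

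| Scenario | Add-on use | Difference (points) | Result |
|---|---|---|---|
| True rate 43% in both arms, add-ons in TDSJ only | 10% | 0.10 × 57 × 0.5 = 2.9 | 4% chance of a significant result favouring TDSJ |
| | 20% | 5.7 | 7% |
| | 50% | 14.3 | 22% |
| 78% vs 43%, add-ons in control only | 10% | 32.2 | power 81.6% |
| | 20% | 29.3 | power 74.2% |
| | 30% | 26.5 | power 65.7% |
| 78% vs 43%, add-ons in both | 30% | 29.8 | power 77.4% |

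The first three rows compare with a nominal 2.5% in that direction; the others compare with 87.6%. Add-on use can therefore create a spurious advantage or hide a real one, depending on which arm uses more.

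**The case against.** The strongest objection is about reading. The disease whose treatment needs are mentioned could be a concomitant disease: the sentence begins with patients who have other diseases, the next sentence concerns those diseases, and progression of AS is then dealt with through withdrawal. On that reading the two routes largely disappear. This stands as a genuine ambiguity. It does not remove the point, because drugs for other diseases are also mentioned separately, and on either reading nothing stated keeps a drug that acts on the primary scores out of the 8 weeks. A full protocol might list restricted drugs, but the article does state a co-treatment rule, and that rule is permissive.

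Several stronger readings are tempting and are not supported:

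- **That recording is the only condition.** Section 3.3 also requires real need, though without a criterion.
- **That section 3.3 reverses sections 2.3.3 and 2.3.4.** Those are entry criteria; they set no rule during treatment that could be reversed.
- **That section 4.5 takes the week-8 value as it stands.** It names the tests and the intent-to-treat principle. It does not say whether the week-8 value or the change is compared, or how values after an addition are treated.
- **That the trial cannot answer its question.** Comparing arms as randomised, whatever was added, is a recognised treatment-policy question. Preferring another estimand is a choice, not the correction of an error. Excluding progressors, however, does not fit that policy.

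The size and direction of the bias are also assumed. At the low end the inflation is negligible.

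**Conclusion.** The point holds in limited form. The stated co-treatment rule leaves open whether treatment for AS may be added without withdrawal, does not extend the entry restrictions through the treatment period, and sends progressors to an exclusion that conflicts with section 4.5. The possible difference in add-on use between arms rests on the absence of double-blinding and on an NSAID being present in one arm only.

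The bias could run either way, and its actual size cannot be known from the documents. A two-sided false-positive rate of about 5.5–17.5% per outcome, against 5%, requires the assumed net excess of 10–30% in the TDSJ arm and an add-on effect of 0.5–0.8 SD. The loss of power with an excess in the control arm rests on the assumed conversion of half the non-responders who take an add-on. A reader might infer that the design favours TDSJ; the documents do not establish that.

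**What to change.** 1. Reconcile section 3.3 with sections 2.3.3, 2.3.4 and 4.5. State whether treatment that acts on the primary scores may be added without withdrawal, and whether the disease in question is AS or another condition. Which co-treatments are allowed is for the sponsor to decide.
2. Remove the conflict between excluding progressors and analysing all randomised participants. Keep everyone who adds treatment or progresses in follow-up and in the analysis.
3. Date the start of each addition from the records section 3.3 already requires. Apply one pre-specified rule, the same in both arms, to scores obtained afterwards.
4. Report add-on use by arm. Beside the as-observed intent-to-treat analysis, add a sensitivity analysis that does not credit post-add-on scores to the randomised treatment, for example by ranking them as unfavourable. Interpret it with care: the decision to add a drug may itself depend on knowledge of the arm.

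The cost is some wording and one extra analysis on data already recorded. The TDSJ result may look slightly less favourable in the sensitivity analysis.

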### 2.4. Sample size

The sample size calculation was performed using PASS 15 software (https://www.ncss.com/),^[7]^ with α = 0.05 (2-tailed test). The sample size was N_1_ in the treatment group and N_2_ in the control group. According to the current clinical efficacy statistics of TCM in the treatment of AS, the effective rate of the treatment group was P_1_ = 78%, while the control group P_2_ = 43%. Using the Z test, H_0_: P_1_–P_2_ = 0. H_1_: P_1_–P_2_ = D_1_ ≠ 0, calculated using the approximate normal method, N_1_ = N_2_ = 36. Considering the loss of cases, if the loss rate is 10%, and each group increases by 4 people, the final sample size is 40 cases in the treatment group and the control group, for a total of 80 cases.

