### 4.5. Statistical analysis

SPSS 28.0 software (https://www.ibm.com/spss) will be used by professionals blinded to trial grouping for statistical analysis of data. Efficacy and safety analyses will be based on the intent-to-treat principle of analysis of all randomized participants. Measurement data that conform to normal distribution are represented by mean and standard deviation (‾ *x ± s*), and measurement data that are not normally distributed are represented by median and quartile (M[Q _25_, Q _75_]). Qualitative data is expressed as a %. If the data obey the normal distribution and the variance is homogeneous, the *t* test would be used for comparison; if the data does not conform to the normal distribution or the variance is unequal, the nonparametric test should be used for comparison. A 2-tailed test will be used, and *P* < .05 indicated a statistically significant difference.

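### The rule that patients who progress and withdraw become excluded cases (Section 3.3) conflicts with the promised analysis of all randomized participants (Section 4.5)

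*Protocol article*

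**What the plan says.** Section 3.3 (Combined treatment regulations) first allows withdrawal: "If disease progresses during the study, participants can withdraw from the study and use other treatments". It then says how the patient is handled: "This case will be treated as an excluded case". The same sentence asks the patient to finish the assessments where feasible.

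Section 4.5 (Statistical analysis) defines who is analysed: "Efficacy and safety analyses will be based on the intent-to-treat principle of analysis of all randomized participants".

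Three other parts of the article bear on this:

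- Section 4.1 names four primary outcomes (pain on a visual analogue scale, BASDAI, BASFI and the TCM syndrome score), measured at weeks 0 and 8 only.
- Section 2.5 states that double-blinding is impossible. Only outcome assessors and data curators are kept unaware of the assignment.
- Section 2.4 plans 40 patients per arm: 36, plus 4 for an assumed 10% loss.

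**The concern.** A randomized patient who progresses and withdraws is excluded under Section 3.3 and analysed under Section 4.5. This is not a detail left to an analysis plan. The article states a rule for these patients, and the rule clashes with the article's own analysis population.

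If the exclusion is applied to the comparison, it does harm for three reasons:

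- The trigger comes after randomization and is a failure of treatment, so the patients removed tend to be those who did worst.
- One arm takes a decoction and the other takes capsules and tablets. Patients and treating clinicians therefore know the arm when withdrawal is decided, and blinding the assessors does not protect against that.
- The two regimens are very different, so equal progression withdrawal cannot be presumed. The arm that loses more failures looks better than it is, and this could be either arm.

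The text as it stands also leaves two analysis populations open, and the choice between them could be made after the data are seen.

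**Working it through.** **1. The two statements applied to one patient.** Take a randomized patient who progresses in week 5 and withdraws.

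| Source | Status of the patient |
|---|---|
| Section 3.3 | excluded case, assessments completed where possible |
| Section 4.5 | in the efficacy and safety analyses |

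No other section limits the exclusion to a per-protocol set, equates it with stopping study treatment, or says how such a patient enters the week-8 comparison.

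**2. The plan's own figure.** From Section 2.4: effective rates 0.78 and 0.43, two-sided α = 0.05, normal approximation. Power is not stated, and 90% is the value that reproduces the figure with unpooled variance:

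n = (1.960 + 1.282)² × [0.78 × 0.22 + 0.43 × 0.57] / 0.35² = 10.507 × 0.4167 / 0.1225 = 35.74, so 36 per arm.

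With 10% loss, 36 / 0.90 = 40 per arm. The stated sample size reproduces and is not in question. Each excluded patient is 1/40 = 2.5% of an arm.

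**3. Illustration with a response rate.** The article gives no progression rate. Assumptions: true response is 60% in both arms, every progressor is a non-responder, and all progressors are excluded. The observed rate in an arm with exclusion fraction f is then 0.60 / (1 − f).

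| Excluded, arm A v arm B | Observed rates | False difference |
|---|---|---|
| 10% v 10% | 66.7% v 66.7% | 0 points |
| 10% v 5% | 66.7% v 63.2% | 3.5 points |
| 15% v 5% | 70.6% v 63.2% | 7.4 points |
| 20% v 5% | 75.0% v 63.2% | 11.8 points |

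Under the planning rates of 78% v 43%, a true difference of 35 points, the direction depends on which arm loses more:

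- 15% excluded from treatment and 5% from control: 0.78/0.85 − 0.43/0.95 = 91.8% − 45.3% = 46.5 points.
- 5% excluded from treatment and 15% from control: 0.78/0.95 − 0.43/0.85 = 82.1% − 50.6% = 31.5 points.

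A response rate appears only in the sample size calculation and is not a primary outcome. These figures show the mechanism, not the expected bias in the trial's endpoints.

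**4. Illustration with a continuous score.** Simulation with 20,000 runs, 40 per arm, standard normal scores, no true effect and a two-sided t test at 5%. Patients are removed in order of a withdrawal ranking that correlates with the outcome to the degree shown. Ranges are from repeated runs.

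| Removed | Correlation 0.3 | Correlation 0.5 | Exactly the worst values |
|---|---|---|---|
| 10% v 5% | 5.3% | about 6% | 9.5-9.7% |
| 15% v 5% | 5.4-5.7% | 6.5-6.9% | 15.2-15.5% |
| 20% v 5% | 6.2-6.3% | 8.3-9.0% | 23.4-24.1% |

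Part of the worst-case inflation has nothing to do with imbalance. Removing exactly the worst 5% from both arms already gives about 7%, and the worst 10% from both about 8%, because trimming shrinks the standard deviation.

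**The case against.** The strongest defence is that the phrase is loose wording for coming off study treatment. Section 3.3 concerns concomitant treatment and names no analysis set, Section 4.5 is explicit, and the request for assessments in Section 3.3 makes little sense if the patient is to be discarded. This reading is possible, and on it there is no conflict. But the preceding sentence already covers withdrawal, so the phrase adds something about how the case is treated, and the article never says that it means discontinuation only. The wording needs correcting on either reading.

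The second defence is that the size is assumed, and this stands. The only loss figure in the article is 10% overall, equal rates give no false difference under no true effect, and the largest type I error figures require progression to rank the final score perfectly.

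A reader might infer three stronger things that the documents do not support:

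- That treatment failures will certainly be removed from the comparison. The text permits this but does not establish it.
- That the bias could not be repaired afterwards. Section 3.3 asks for assessments where possible, so data to keep many of these patients would often exist. Only those with no later value are lost, and that is ordinary missing data.
- That the plan must contain an imputation rule or an extra visit at stopping. Handling of missing values is commonly left to an analysis plan, which is not shown here.

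**Conclusion.** The point stands as a contradiction in the stated rules: Sections 3.3 and 4.5 cannot both be followed literally for a patient who progresses and withdraws. If Section 3.3 governs the analysis, the exclusion depends on outcome and can favour either arm.

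The size cannot be derived from the article. At the assumed withdrawal rates of 10%, 15% and 20% against 5%, the false difference in a response rate is 3.5, 7.4 and 11.8 points. Type I error for a continuous score runs from about 6%, 7% and 8-9% (correlation 0.5) to about 10%, 15% and 24% as a worst case, and a correlation of 0.3 gives only 5-6%. The need for correction rests on the contradiction and not on any one of these figures.

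**What to change.** Reconcile Sections 3.3 and 4.5. In Section 3.3, replace the exclusion phrase with wording to this effect: such patients are recorded as having discontinued study treatment; they remain in the all-randomized analysis set in their assigned arm; and their week-8 primary outcomes, obtained as far as possible, enter the primary analysis whatever treatment they then receive. Week 8 should be named, because Section 3.3 asks for assessments without giving a time and Section 4.1 has no other time point after baseline. State that any exclusion applies only to a secondary per-protocol analysis.

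Handling of week-8 values that are still missing can be left to the analysis plan. The rule on when patients may stop is not touched.

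The cost is a sentence or two of text and the effort to obtain week-8 assessments after withdrawal, which Section 3.3 already largely asks for. The sample size stays at 80. The downside is that the estimate may become less favourable to the arm with more progression.

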## 4. Outcome measures

### 4.1. Primary outcome

Visual analogue scale, bath ankylosing spondylitis disease activity index, bath ankylosing spondylitis functional index, and TCM syndrome scores will be primary indicators, which will be tested at 0th and 8th weeks of treatment.

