## Abstract

**Methods::**

In this randomized controlled trial, 80 eligible patients were randomly assigned in a 1:1 ratio to a treatment group TDSJ and a control group (celecoxib capsules in combination with thalidomide tablets) for 8 weeks. Visual analogue scale, bath ankylosing spondylitis disease activity index, bath ankylosing spondylitis functional index, and traditional Chinese medicine syndrome scores will be used as primary indicators. Erythrocyte sedimentation rate, C-reactive protein, spinal mobility (figure-ground distance, occipital tubercle-wall distance, Schober test) will be used as secondary indicators. Vital signs (respiration, heart rate, body temperature, blood pressure, electrocardiogram), blood routine, urine routine, stool routine, liver function, and renal function will be used as safety indicators. The primary and secondary indicators will be detected at 0th and 8th week, while safety indicators at 0th, 4th, and 8th week.

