### 4.3. Safety outcomes

Vital signs (respiration, heart rate, body temperature, blood pressure, electrocardiogram), blood routine, urine routine, stool routine, liver function, and renal function will be safety indicators, which will be tested at 0, 4, and 8 weeks of treatment. If an adverse event occurs, the clinical investigator will record it in detail on the case report form (including symptoms, time of onset, duration, examination and results). Serious adverse reactions will be reported to the Ethics Committee of the First Affiliated Hospital of Henan University of Chinese Medicine and rescue procedures will be initiated immediately.

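### Efficacy is scheduled only at weeks 0 and 8 although a week-4 safety assessment exists, so a patient lost before week 8 has no scheduled post-baseline efficacy value: a cheap improvement, not an error

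*Protocol article*

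**What the plan says.** The abstract of the protocol article sets the schedule: "The primary and secondary indicators will be detected at 0th and 8th week, while safety indicators at 0th, 4th, and 8th week". Section 4.1 repeats it for the four primary measures (VAS, BASDAI, BASFI and the TCM syndrome score), "which will be tested at 0th and 8th weeks of treatment", and section 4.2 does the same for the secondary measures. Section 4.3 places the safety tests at an extra time point, "which will be tested at 0, 4, and 8 weeks of treatment".

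Three other statements bear on this:

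- Section 2.4 expects some loss: "if the loss rate is 10%, and each group increases by 4 people".
- Section 4.5 sets the analysis set: "Efficacy and safety analyses will be based on the intent-to-treat principle of analysis of all randomized participants".
- Section 3.3 lets patients whose disease progresses withdraw and use other treatment, and adds: "This case will be treated as an excluded case and the patient will be asked to complete relevant examinations and assessments as far as possible".

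**The concern.** With one post-baseline efficacy time point, a patient who leaves before week 8 contributes a baseline value and nothing else that the schedule requires. The analysis of that patient must then rest on imputation from baseline, or the patient drops out of the comparison. An analysis plan can choose how to handle the gap, but it cannot supply a week-4 score that was never taken.

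The loss need not be harmless. Section 3.3 foresees withdrawal because of progression, which is related to outcome. The two regimens differ greatly and section 2.5 says double-blinding is impossible, so unequal loss is plausible, although the documents give no rates by arm. If one arm loses more of its worst patients, its completers look better than the arm as randomized.

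**Working it through.** **The plan's own figures.** Section 2.4 gives 78% v 43%, two-sided α of 0.05 and 36 per arm. Power is not stated, so 90% is an assumption. With unpooled variance:

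n = (0.78×0.22 + 0.43×0.57) × (1.960 + 1.282)² / 0.35² = 35.7, rounded up to 36.

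Then 36 / (1 − 0.10) = 40 per arm. The planned loss is 4 per arm, 8 of 80, and leaves the 36 the trial was sized on. The issue is therefore possible bias, not sample size.

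**Size of the bias, by formula.** Assumed, not in the documents: standardised normal scores with higher meaning worse, correlation 0.5 of baseline with week 4 and with week 8, 0.7 between week 4 and week 8, no true effect, and the patients worst at week 4 lost before week 8.

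If the worst fraction d is lost, the week-4 mean of those remaining shifts down by m(d) = φ(z)/(1 − d), where φ is the standard normal density at the cut point z:

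- m(5%) = 0.1031/0.95 = 0.109
- m(10%) = 0.1755/0.90 = 0.195
- m(15%) = 0.2332/0.85 = 0.274
- m(20%) = 0.2800/0.80 = 0.350

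The shift carries to week 8 with weight 0.7. Baseline adjustment takes back about 0.5 × 0.5 = 0.25. So the completer bias is about 0.45 × [m(d₁) − m(d₂)]:

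- 10% v 10%: 0
- 10% v 5%: 0.45 × 0.086 = 0.039 SD
- 15% v 5%: 0.45 × 0.166 = 0.075 SD
- 20% v 5%: 0.45 × 0.241 = 0.109 SD

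**Simulation, 40 per arm.** Repeated runs of 4,000 to 6,000 trials per scenario agree. Simulation error is about 0.20/√4000 = 0.003 SD. Signs are dropped; the bias favours the arm with more loss.

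| Loss mechanism | Loss by arm | Completer ANCOVA bias (SD) | Bias using week 4 (SD) |
|---|---|---|---|
| Week-4 status, all lost after week 4 | 10% v 10% | 0.002 | 0.001 |
| Same | 10% v 5% | about 0.04 | about 0 |
| Same | 15% v 5% | 0.07 to 0.08 | about 0 |
| Same | 20% v 5% | 0.11 to 0.12 | about 0 |
| Half lost before week 4 | 10% v 5% | about 0.04 | 0.015 to 0.025 |
| Half lost before week 4 | 20% v 5% | 0.11 to 0.12 | about 0.05 |
| All lost before week 4 | 20% v 5% | 0.116 | 0.116 |
| Week-8 state | 10% v 5% | 0.070 | 0.048 |
| Week-8 state | 20% v 5% | 0.194 | 0.136 |

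Where half the losses precede week 4, the share removed runs from 1 − 0.025/0.045 = 44% to 1 − 0.015/0.040 = 62% across runs, so about half to 60%. Where loss depends on the week-8 state it is 1 − 0.048/0.070 = 31% and 1 − 0.136/0.194 = 30%. The standard error of the treatment difference is about 0.20 SD with or without week 4.

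**The case against.** Baseline plus end of treatment is a coherent schedule for an 8-week trial and does not in itself conflict with intent-to-treat. How missing values are handled, and which model is used, may properly sit in an analysis plan that is not shown. All of this stands, and it is why the point is an improvement and not an error.

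A reader might infer that every early withdrawal leaves nothing after baseline. The documents do not support that: section 3.3 asks patients who withdraw for progression to complete assessments as far as they can. What remains is that this request is best effort, covers one reason for leaving, and names no scale and no time.

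A reader might also take 0.12 SD as the bias to expect. Section 2.4 adds the same 4 patients to each arm, and at equal 10% loss the bias is about zero. Unequal loss is an assumption, and even 0.12 SD is 0.12/0.20 = 0.6 of a standard error; 0.04 SD is 0.2. If loss is random or depends only on baseline, there is nothing to correct.

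Nor is near-complete removal of the bias the general result. It needs every lost patient to reach week 4 and loss to depend on the observed week-4 score. The documents do not say when losses fall, so week-4 data could exist for anywhere from 0 to 8 of the 8 expected losses.

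Finally, a week-4 score cannot help patients who are excluded by rule. That is right, and it makes the tension between sections 3.3 and 4.5 part of the remedy.

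**Conclusion.** The point holds as a cheap improvement. The schedule fixed in the abstract and sections 4.1 and 4.2 takes no efficacy measure between weeks 0 and 8, while section 4.3 has an assessment at week 4. Patients lost in between have no scheduled efficacy value for the analysis promised in section 4.5.

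The gain ranges from nothing to the removal of about 0.12 SD of bias. It is nil at equal 10% loss or if all losses precede week 4, partial if some do or if loss follows the week-8 state, and nearly complete only in the favourable case. These sizes rest on the assumed correlations and loss patterns, not on figures in the documents.

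Separately, treating progression withdrawals as excluded cases (section 3.3) and analysing all randomized participants (section 4.5) do not agree as written and must be reconciled.

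**What to change.** 1. Collect VAS, BASDAI, BASFI and the TCM syndrome score at the existing week-4 assessment, with the same assessor blinding as at week 8.
2. Keep week 8 as the primary time point, so that week 4 adds no further primary comparison.
3. For each of these measures, estimate the week-8 difference in all randomized patients with a mixed model for repeated measures: baseline score, treatment, visit and treatment by visit, with unstructured covariance over weeks 4 and 8.
4. Reconcile sections 3.3 and 4.5 so that data already collected from patients who withdraw for progression, including the week-4 scores, stay in the analysis.

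The cost is a few minutes of scoring per patient and a small amendment. No new visit or laboratory test is needed, and the sample size does not change.
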